# DECIDER: prospective randomized multicenter phase II trial of low-dose decitabine (DAC) administered alone or in combination with the histone deacetylase inhibitor valproic acid (VPA) and all-*trans* retinoic acid (ATRA) in patients >60 years with acute myeloid leukemia who are ineligible for induction chemotherapy

**DOI:** 10.1186/s12885-015-1432-5

**Published:** 2015-05-26

**Keywords:** Acute myeloid leukemia, Low-dose decitabine, Valproic acid, All-*trans* retinoic acid, Elderly patients

## Abstract

**Background:**

Acute myeloid leukemia (AML) is predominantly a disease of older patients with a poor long-term survival. Approval of decitabine (DAC) in the European Union (EU) in 2012 for the treatment of patients with AML ≥65 years marks the potential for hypomethylating agents in elderly AML. Nevertheless the situation is dissatisfactory and the quest for novel treatment approaches, including combination epigenetic therapy is actively ongoing. The given randomized trial should be helpful in investigating the question whether combinations of DAC with the histone deacetylase (HDAC) inhibitor valproic acid (VPA) and/or all-*trans* retinoic acid (ATRA), which *in vitro* show a very promising synergism, are superior to the DAC monotherapy. The accompanying translational research project will contribute to find surrogate molecular end points for drug efficacy and better tailor epigenetic therapy. An additional aim of the study is to investigate the prognostic value of geriatric assessments for elderly AML patients treated non-intensively.

**Methods/Design:**

DECIDER is a prospective, randomized, observer blind, parallel group, multicenter, Phase II study with a 2x2 factorial design. The primary endpoint is objective best overall response (complete remission (CR) and partial remission (PR)). The target population is AML patients aged 60 years or older and unfit for standard induction chemotherapy. Patients are randomized to one of the four treatment groups: DAC alone or in combination with VPA or ATRA or with both add-on drugs. One interim safety analysis was planned and carried out with the objective to stop early one or more of the treatment arms in case of an unacceptable death rate. This analysis showed that in all treatment arms the critical stopping rule was not reached. No important safety issues were observed. The Data Monitoring Committee (DMC) recommended continuing the study as planned. The first patient was included in December 2011. A total of 189 out of 200 planned patients were randomized since then (status 31.12.2014).

**Trial registration:**

ClinicalTrials.gov identifier: NCT00867672 (registration date 23.03.2009); German clinical trials registry number: DRKS00000733 (registration date 19.04.2011).

## Background

Acute myeloid leukemia (AML) of the older patient constitutes a major unmet clinical need since the large majority will not be found eligible for induction chemotherapy. Reasons for this decision include host factors (comorbidities, reduced performance status, functional limitations due to age), often leading to poor tolerance of repeated chemotherapy courses, as well as the unfavorable biology of this disease in older patients. Among low dose cytarabine, azacitidine or best supportive care, the hypomethylating agent (HMA) decitabine (DAC) represents one of the therapeutic options for these patients providing effectiveness, good tolerability and maintenance of quality of life. In this trial, we ask whether a combination of DAC with the histone deacetylase inhibitor VPA and/or ATRA is able to increase the objective best response rate to DAC alone in AML of the elderly.

### Rationale for combination of DAC und VPA in AML

Since the pioneering discovery by Cameron et al. [1] of a synergism between demethylation and histone deacetylase (HDAC) inhibition in the re-expression of silencing genes, investigations have been advanced in pre-clinical and clinical studies using the two DNA methyltransferase inhibitors available (azacitidine and decitabine) in combination with different HDAC inhibitors. Research of the additional effects of HDAC inhibitors appears particularly important and promising, since both mouse data [2, 3] and *ex vivo* results [4] have given clear indications that a combination of demethylation agents with HDAC inhibitors may exhibit beneficial effects on the normal hematopoiesis as well as on active suppression of the malignant clone. Three clinical studies investigated the combination of DAC and VPA in AML/MDS patients. In a large Phase II study performed at the MD Anderson Cancer Center (MDACC) [5], DAC (10 daily one hour infusions) was given concomitantly with escalating doses of VPA over 10 days to 54 patients. A response rate of 22 % was observed (10 CR, 2 CR with incomplete platelet recovery). Based on the toxicity profile, this combination was judged safe and active. Transient reversal of aberrant epigenetic marks was noted. In a study coordinated by the Ohio State University [6], 25 patients were treated with DAC for 10 days, and escalating VPA doses on days 5–21. A response rate of 44 % was reported (4 CR, 4 CR with incomplete platelet recovery, 3 PR). Overall, non-hematologic toxicity was limited, however with dose-limiting encephalopathy noted in several patients. Also in that study, epigenetic marks were studied in conjunction with treatment. Re-expression of estrogen receptor (ER) was shown to be associated with the clinical response. ER promoter demethylation, global DNA hypomethylation, depletion of DNA methyltransferase enzyme, and histone hyperacetylation were observed. A large randomized trial investigating clinical response and epigenetic modulation of DAC with or without VPA has been recently published by the MDACC [7]. The study could not show a benefit of the simultaneous addition of VPA to DAC in MDS/AML patients suggesting that different scheduling regimes have to be explored.

### Rationale for the combination of DAC and ATRA in AML

An intriguing rationale of the potential sensitization of non-M3 blasts to the effects of ATRA by pre-treatment with chemotherapy or azanucleosides has driven important lines of investigation. Several large clinical studies have addressed the role of ATRA when given in combination with high-dose chemotherapy: Schlenk and colleagues could show that the addition of ATRA to induction therapy in AML patients >60 years resulted in a survival benefit [8]. However, large studies by the Medical Research Council and MDACC did not show an additional effect of ATRA [9–11], which may be due to the timing of the dosing and/or different patient populations [12].

We have begun to address the question of a combination of DAC + ATRA by implementing a four week treatment of ATRA in a multicenter study during the second course of DAC, in patients showing sensitivity to DAC alone. Comparison of the overall survival of patients who did or did not receive ATRA during the second course did not reveal a superior outcome for patients who received ATRA [13]. The study showed feasibility of the combination DAC + ATRA in the clinical setting and comparability of its safety profile to that of DAC given alone. Furthermore, we could recently demonstrate that AML cell lines treated *in vitro* with DAC (either alone or in combination with ATRA or the HDAC inhibitor entinostat) showed enhanced *in vitro* differentiation in the presence of the retinoid, providing an additional rationale to combine ATRA with the HMA DAC [14]. Thus, taken together these data suggest that a controlled setting is needed to investigate this research question accurately.

### Rationale for the combination of VPA and ATRA in AML

Preclinical results of several groups have demonstrated that VPA alters the sensitivity towards ATRA, providing a strong rationale to advance this approach also clinically [15, 16]. Several groups combined VPA with ATRA in the treatment of MDS and AML [16–18] and showed good tolerability of this combination. In the study of the MDACC a total of 53 patients with high-risk MDS or refractory/relapsed AML were treated with a three-drug combination: azacitidine, VPA and ATRA. The overall response rate was 42 %. In previously untreated older patients, the response rate was 52 %. The treatment was shown to be safe and associated with induction of global DNA hypomethylation and histone acetylation [19]. However, the role of the drug combinations has not been tested in a rigorous fashion using a randomized design. This appears important in the context of a study with DAC, since the available evidence suggests that combinations of this HMA with a second epigenetic drug and an inducer of differentiation may reveal efficacy that is superior to the HMA alone.

Thus, in this trial, we ask whether a combination of DAC with the HDAC VPA or ATRA or with both add-on drugs is able to increase the objective best response rate to DAC alone in AML of the elderly. The hypothesis that the combination is more active than single-agent DAC will be investigated in a randomized setting.

## Methods/Design

### Study design and setting

This is a prospective, randomized, observer blind, active control, parallel group, multicenter, phase II study. The objective of the trial is the investigation of efficacy and safety of the histone deacetylase inhibitor (VPA) and all-*trans* retinoic acid (ATRA) as add-on to the epigenetically active drug decitabine (DAC) in older and unfit acute myeloid leukemia (AML) patients.

The trial has a 2x2 design randomizing the patients to the following four treatment arms: DAC, DAC + VPA, DAC + ATRA, DAC + VPA + ATRA. The effect of VPA will be investigated by comparing the combined treatment arms (DAC + VPA) and (DAC + VPA + ATRA) as experimental group versus the combined treatment arms (DAC) and (DAC + ATRA) as control group, and the effect of ATRA will be investigated by comparing the combined treatment arms (DAC + ATRA) and (DAC + VPA + ATRA) as experimental group versus the combined treatment arms (DAC) and (DAC + VPA) as control group.

Trial sites are located in Aachen, Berlin, Bochum, Braunschweig, Bremen, Düsseldorf (two sites), Esslingen, Frankfurt, Freiburg, Hagen, Halle, Hamm, Hannover, Jena, Koblenz, Lahr, Lebach, Leipzig, Lüdenscheid, Marburg, München, Münster, Offenburg, Ravensburg, Tübingen, Ulm, and Villingen-Schwenningen.

The study and all participating sites were approved by the central ethics committee (University of Freiburg, 76/10) and the respective local ethics committees. Patient’s written consent to participate in this clinical trial and translational research program was obtained prior to any study-specific procedures. The identifying number of the DECIDER trial in ClinicalTrials.gov registry is NCT00867672 and in German clinical trials registry DRKS00000733.

### Study population

The target population of this trial represents patients older than 60 years with AML according to WHO (≥20 % blasts in the peripheral blood or bone marrow) not qualifying for, or not consenting to, standard remission-induction chemotherapy or immediate allografting. Key inclusion criteria are: patient’s written informed consent; 60 years or older at time of informed consent; patients with primary or secondary AML according to WHO who are not expected to benefit from standard remission-induction chemotherapy; <30.000 leukocytes/μl and performance status ECOG 0, 1, 2. Key exclusion criteria are: Acute promyelocytic leukemia (APL), AML of FAB subtype M3; previous remission-induction chemotherapy for MDS or AML, previous allografting; previous treatment with DAC, 5-azacytidine, VPA or another histone deacetylase inhibitor, or ATRA; “low-dose” chemotherapy (e.g., hydroxyurea, cytarabine (Ara-C), melphalan, clofarabine etc.) within four weeks prior to DAC treatment, except for cytoreduction of leukocytosis ≥30.000/μl with hydroxyurea or Ara-C as proscribed by the study protocol; treatment with tyrosine kinase inhibitors, immunomodulating agents or other investigational AML treatment within the last four weeks or in a time period of drug half-life x 5 (whatever is shorter) before the first administration of DAC; treatment with cytokines within the previous four weeks. Further exclusion criteria are related to general medical conditions or contraindications to administration of investigational products according to Summary of Product Characteristics.

### Study treatment and procedures

Study treatment in the four study arms Fig. 1 is as follows: (DAC) intravenous decitabine 20 mg/m^2^ over 1 h, 5 days (total dose 100 mg/m^2^), repeated every 4 weeks; (DAC + VPA) intravenous decitabine 20 mg/m^2^ over 1 h, 5 days (total dose 100 mg/m^2^), repeated every 4 weeks, and VPA (p.o.) from day 6 of first cycle continuously throughout all treatment cycles in a dose to achieve a VPA serum level between 50 to 110 mg/l; (DAC + ATRA) intravenous decitabine 20 mg/m^2^ over 1 h, 5 days (total dose 100 mg/m^2^), repeated every 4 weeks and ATRA (45 mg/m^2^ p.o.) from day 6 to day 28 of each treatment cycle; (DAC + VPA + ATRA) intravenous decitabine 20 mg/m^2^ over 1 h, 5 days (total dose 100 mg/m^2^), repeated every 4 weeks and VPA (p.o.) from day 6 continuously throughout all treatment cycles in a dose to achieve a VPA serum level between 50 to 110 mg/l and ATRA (45 mg/m^2^ p.o.) from day 6 to day 28 of each treatment cycle. Treatment cycles are repeated until relapse/progression, hematopoietic stem-cell transplantation, ongoing cytopenia, other unacceptable toxicity or patient’s death. Response assessment is performed at the end of the cycles 2, 4 and 6, and thereafter every third cycle. Study visits are carried out at least once a month during the treatment and every three months after treatment discontinuation until 12 months after randomization of the last patient.

**Fig. 1 Fig1:**
[figure not shown]
Trial flow. *If WBC ≥ 30.000/μl: Hydroxyurea (HU) or Ara-C until WBC < 30.000/μl. CR = complete remission; PR = partial remission; ALE = antileukemic effect; SD = stable disease

### Study endpoints

The primary endpoint is the objective best overall response, defined as complete remission (CR) or partial remission (PR). Patients are counted as objective responders if they achieve a CR or a PR. All other patients are counted as non-responders. Secondary endpoints for the evaluation of efficacy are the following: (1) the overall best response defined as CR, PR, or antileukemic effect (ALE). Patients are counted as responders if they achieve a CR, PR or ALE. All other patients are counted as non-responders. The determination of CR, PR, and ALE will be performed according to the standard criteria [20, 21], (2) the progression free survival (PFS) time from randomization until relapse/progression or death. For patients being progression-free and alive at the end of the study, the PFS time will be censored at the time of the last evaluation of bone marrow, (3) overall survival (OS) time from randomization until death of the patients. For patients being alive at the end of the study, the OS time will be censored at the time of the last visit or follow-up contact, (4) quality of life of the patients using the EORTC QLQ-C30 Quality of Life Questionnaire, (5) number of nights in hospital. Further secondary endpoint for evaluation of the treatments is safety and toxicity, which are evaluated by means of adverse events (AEs) occurring from the first administration and until 4 weeks after the last administration of the study treatment, death and laboratory assessments.

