### Statistical analysis

The primary efficacy analysis of this clinical trial will be conducted according to the intention-to-treat principle. This means that the patients will be analyzed in the treatment arms to which they were randomized, irrespective of whether they refused or discontinued the treatment or whether other protocol violations are revealed. The analysis of the effects of the different treatment schedules (VPA vs. no VPA and ATRA vs. no ATRA) with respect to the primary endpoint objective best overall response will be performed with a logistic regression model. The treatment effects will be tested using the Wald test at a one-sided significance level of 10 %, and as estimates of the effect sizes the odds ratios will be given with 95 %-confidence intervals. A multiplicative interaction effect between VPA and ATRA will be included in the logistic regression model and its size will be estimated with 95 %-confidence interval. The analysis of the treatment effects with respect to the secondary endpoints PFS and OS will be performed with the Cox model. The analysis of the treatment effects with respect to the secondary endpoint overall best response (CR, PR and ALE) will be performed with a logistic regression model. The PFS rates and the OS rates of the different treatment arms will be estimated by the Kaplan-Meier method, and the ORR of the different treatment arms will be estimated as relative frequencies. For evaluating QOL, scores will be calculated according to Fayers et al., 2001 [25]. At the different time points during follow-up changes in relation to baseline will be calculated. With respect to the secondary endpoints QOL and number of nights in hospital, the treatment groups will be compared descriptively.

Safety is analyzed in the safety population including all randomized patients who received at least one dose of study medication, and patients are analyzed according to the received treatment. AEs are coded using Medical Dictionary for Regulatory Activities (MedDRA). The incidence of AEs is calculated as the number of patients who experienced at least one AE of a certain category as a percentage of the total number of patients in the safety population.

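### The adverse-event window can run up to 23 days longer with ATRA or VPA than with DAC alone, so crude AE percentages should be accompanied by a time-adjusted comparison

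*Protocol article*

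**What the plan says.** Under Study endpoints, safety and toxicity is a secondary endpoint for evaluating the treatments. It is assessed through "adverse events (AEs) occurring from the first administration and until 4 weeks after the last administration of the study treatment", together with death and laboratory assessments.

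Under Study treatment and procedures, DAC is infused on 5 days of each 4-week cycle in all four arms. ATRA is taken "from day 6 to day 28 of each treatment cycle". The other add-on is "VPA (p.o.) from day 6 of first cycle continuously throughout all treatment cycles". The number of cycles is not fixed: "Treatment cycles are repeated until relapse/progression, hematopoietic stem-cell transplantation, ongoing cytopenia, other unacceptable toxicity or patient’s death".

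Under Statistical analysis, safety patients are grouped by the treatment they received. "The incidence of AEs is calculated as the number of patients who experienced at least one AE of a certain category", expressed "as a percentage of the total number of patients in the safety population". No part of the article ties the end of the window to the same day in all arms.

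**The concern.** The end of AE counting is tied to each patient's own last dose, and the timing of that dose within the last cycle differs by arm. Lengthening the window can only add patients to an at-least-one-event count. An add-on arm can therefore show a higher percentage than DAC alone even if the daily risk of an event is the same.

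The trial is meant to decide whether VPA and ATRA are worth taking into phase III (Sample size). AE percentages by arm will inform that judgement, and part of any excess seen with the add-ons could come from the counting rule.

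**Working it through.** The article states no window length or AE rate per arm, so there is no figure of its own to reproduce here. The planned sample size does not enter the argument.

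**Inputs**
- Tail after the last administration: 28 days (Study endpoints).
- Cycle length: 28 days (Study treatment and procedures).
- Last DAC day in a cycle: day 5. This is inferred from 5 infusion days and add-ons starting on day 6.
- Last add-on day in a cycle: day 28 for ATRA as stated. VPA is continuous, so up to day 28.

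**Window length.** After c cycles, the window from first dose closes on day 28(c − 1) + d + 28, where d is the last dosing day of the last cycle.
- DAC alone, d = 5: day 5 + 28 = 33 of the last cycle.
- Add-on taken to the end of the cycle, d = 28: day 28 + 28 = 56 of the last cycle.
- Difference: 56 − 33 = 23 days, whatever the number of cycles. Measured from the end of the 28-day cycle, follow-up is 5 versus 28 days.

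**Effect on a crude percentage (illustration).** Assume the same constant hazard in all arms and a category that reads 30% with DAC alone. Neither assumption comes from the article. With windows T0 and T1, the add-on percentage is 1 − (1 − 0.30)^(T1/T0). For one cycle this is 1 − 0.70^(56/33) = 45.4%. The last column uses half the gap (11.5 days), to allow for add-ons stopped early and for deaths.

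| Cycles | DAC alone, days | Add-on maximum, days | Ratio | Add-on %, full gap | Add-on %, half gap |
|---|---|---|---|---|---|
| 1 | 33 | 56 | 1.70 | 45.4 | 38.2 |
| 2 | 61 | 84 | 1.38 | 38.8 | 34.6 |
| 4 | 117 | 140 | 1.20 | 34.7 | 32.4 |
| 6 | 173 | 196 | 1.13 | 33.2 | 31.6 |

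**Range over other base rates, full gap.** A category at 10% with DAC alone would read 16.4% after one cycle and 11.3% after six. One at 50% would read 69.2% and 54.4%. One at 95% would read 99.4% and 96.6%. The excess is small for categories that are rare or nearly universal.

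**Factorial margins.** If AEs are compared by factor, each group without the drug in question still contains one add-on arm. The mean difference is then at most (0 + 23)/2 = 11.5 days.

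**The case against.** The rule is worded identically for every arm, and a 4-week tail after the last dose is a common convention. It follows exposure, and add-on patients really are exposed for longer. Any distortion overstates add-on harm rather than hiding it. The article plans no AE test, and exposure-adjusted summaries are usually left to the analysis plan, which is not shown.

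Most of this stands, and it limits the point. The convention is harmless where arms finish dosing at similar times. Here the time of the last dose depends on arm, and the stated measure takes no account of observation time. That combination is written in the article, so the point does not rest on something left out. Because the comparison is descriptive, no error rate is affected.

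A reader might infer more than the documents support:
- *That every add-on patient is observed 23 days longer.* That is the maximum. Treatment ends on events that can occur in mid-cycle, and the gap is zero for a patient who dies within the shorter window.
- *That death percentages are distorted as well.* The window qualifies AEs, and no death percentage restricted to it is planned. Overall survival and the interim three-month death rule both run from randomization.
- *That the frailest patients are hit hardest, or that differing cycle numbers make matters worse.* The article gives no cycle counts and does not link them to frailty. Differences in cycle number could add to the effect or offset it.

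**Conclusion.** The point holds as a modest one. Applied as written, the window and the dosing days let AE counting run up to 23 days longer with an add-on than with DAC alone, and the crude percentage carries that difference into the between-arm comparison. The direction, under equal hazards, is towards more AEs in the add-on arms.

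The window lengths follow from the article, given a last DAC dose on day 5 and add-ons taken to day 28. The percentage-point figures are illustrations only: they rest on a constant, equal hazard and on assumed base rates. For a 30% category they range from about 15 points (one cycle, full gap) to about 2 points (six cycles, half gap). The documents do not allow a single estimate for this trial, nor the statement that its safety comparison as a whole is invalid. The primary endpoint and sample size are untouched.

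**What to change.** Keep the collection window and the crude percentages. Base between-arm AE comparisons on a time-adjusted measure, either:
- cumulative incidence of the first event of a category from first dose, read at common time points, censored at the end of each patient's AE window and with death as a competing event; or
- events per patient-month of observation.

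As a sensitivity analysis only, count events up to the same day of the last started cycle in all arms and list later events separately. With the collection rule as it stands, about day 33 is the latest day available in every arm. This should not be the main analysis: it leaves only 5 days after an add-on dose on day 28, and so leaves out some late add-on events.

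Longer AE collection with DAC alone is not recommended. With 189 of 200 patients randomized by the end of 2014 (Study status), it would make ascertainment differ within that arm, and visits after treatment stops are only every three months.

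The cost is a little more analysis work, using dosing, event and death dates that the trial needs anyway. Neither measure is assumption-free. Censoring when the window closes is linked to stopping treatment, and a rate per month averages over time on and off drug. Both should be stated alongside the results.
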